### Analgesic use

All postoperative oral and parenteral administered narcotic analgesics will be converted and added up using accepted algorithms [59, 60] and compared after the last treatment day, at discharge and at the outpatient clinic. Total milligrams of acetaminophen and non-steroidal anti-inflammatory drugs (NSAID’s) are reported in the same fashion. At the outpatient visit patients will be asked about their current pain medication use.

### Postoperative blood loss and transfusion incidence

The hemoglobin values from the obtained blood samples at postoperative day one and three will separately be detracted from the preoperative concentration and postoperative day three will be detracted from postoperative day one. An adjustment will be made for the intraoperative blood loss. Indications for transfusion are managed according to the Dutch national blood transfusion guideline [61]. Normovolemic ASA-one patients older than 60 years who lose blood at a single locus will be transfused at 5 mmol/l (8 g/dl). Patients unable to elevate cardiac output for hemodilution are transfused at 6 mmol/l (9.6 g/dl). Incidence of erythrocyte transfusion is noted and compared between groups.

### Postoperative delirium

The DRS-R-98 is considered to be a valid and reliable instrument for delirium diagnosis and documenting delirium severity [49, 62]. It takes a trained nurse or physician five to ten minutes to assess the patient and comprise the DRS-R-98 score, and is ideal for longitudinal delirium follow-up. The sensitivity and specificity of the scale are reported to be 92 % and 86 % respectively. DRS-R-98 scores are compared within and between groups, and newly started psychotropic medication is compared.

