### Randomization

A balanced 1:1 block (size six) randomization stratified by center will be performed directly after surgery, using Research Manager (RM; version 4.5.0.1), a web-based computer program (Fig. 1). A research nurse who is not involved in the study generates the allocation sequence with RM. Intramedullary hip nail (IMHN), dynamic hip screw (DHS) and cannulated screws are grouped for block randomization, as are total hip arthroplasty (THA) and hemiarthroplasty (HA). The intervention group ‘A’ will receive CFC therapy postoperative; the control group ‘B’ will receive standard care. Due to the nature of the study no blinding can exist as patients, family and physicians notice the use and settings of CFC therapy. Physicians randomize participants with a digital logon to the web-based system or the physician can contact the coordinating investigator and he will randomize the included participant (see Table 1 for criteria).The Informant Questionnaire for the Cognitive Decline in the Elderly (IQ-CODE) questionnaire is administered when the clinician has doubts about the cognitive state that may compromise CFC therapy sessions or study measurements (Table 1). Ideally a MMSE would be used for this purpose, however due frequently perceived pain at the accident and emergency A&E department and consequently administered narcotic analgesics, the hetero anamnestic IQ-CODE is used instead. The coordinating investigator contacts the participating hospitals on a daily basis by telephone or physically to ensure adequate and appropriate enrollment of participants and completeness of data. A list of excluded patients will be drafted.

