**Table 4 Tab4:** Outcome assessment points

		Assessment point						
Item	Data collection instrument (unit)	Baseline (A&E department)	Day of surgery	24 h	48 h	72 h	Discharge	6 - 8 weeks (outpatient clinic visit)
Demographics	-	X						
Pre-fracture functional status	NMS, KATZ-ADL	X						X
Delirium risk assessment	DRAS	X						
Cognitive function	IQ-CODE	X						
	MMSE						X	X
Blood loss	Intraoperative loss *(cc’s)*		X					
	Drain output^a^ *(cc’s)*			X	X	X	X	
Outcome								
Pain	NRS	X	X	X	X	X	X	X
Analgesics	Acetaminophen	X				X	X	
	NSAID’s	X				X	X	
	Morphine	X				X	X	
Blood loss	Hemoglobin (mmol/l)	X		X		X		
Transfusion incidence	Number of units						X	X
Delirium	DOS-score	X	X	X	X	X	X	
	DRS-R-98^c^		X	X	X	X	X	
	Pyschotropic medication	X				X	X	
Length of stay^b^	*(Hours)*						X	
Functional outcome	TUGT						X	X
	DEMMI							X
	SPPB							X
	Rehabilitation location						X	X
	Rehabilitation duration						X	X
PROM	EQ-5D-3L							X
	SF-12							X
	Satisfaction questionnaire						X	
Complications	General						X	X
	Therapy related						X	X
Feasibility	Nurse staff questionnaire						At discharge of last patient	

*A&E* accident and emergency, *NMS* New Mobility Score, *IQCODE-N* Informant Questionnaire on the Cognitive Decline in Elderly patients, *MMSE* Mini Mental State Exam, *NRS* numeric rating scale, *PC* packed cells, *DOS* Delirium Observation Screening, *DRS-R-98* Delirium Rating Scale Revised 98, *TUGT* Timed Up and Go Test, *DEMMI* De Morton Mobility Index, *EQ-5D-3*
*L* EuroQol questionnaire, *SF-12* Short Form-12 questionnaire

^a^Including autologous reinfusion. ^b^Start count at admission and at the end of surgery. ^c^: administered when DOS ≥ 3

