### Cryocompression therapy and clinical measurements

Intervention patients start with CFC therapy 6 h postoperative, until 72 h postoperatively. A trained ward nurse will conduct the pain assessments when the patient is in bed or stationary in a chair for at least five minutes. Directly before and directly after CFC therapy vital signs including NRS-pain are measured by the ward nurse, when the patient is prone in bed for at least five minutes before commencing and five minutes after cessation of CFC therapy. In control patients only NRS-pain is measured at the same time as intervention patients would normally be assessed. All pain measurements are continued throughout the first postoperative 72 h for control and intervention patients alike (Table 4). Three times daily DOS-scores [48] will be obtained; in case of a DOS-score higher or equal to three, geriatricians diagnose and subsequently monitor delirium severity with the delirium rating scale revised 1998 (DRS-R-98) [49] on a daily basis or until the score drops below 12.25 out of 39 (Table 4). Time and amount of administered (psychotropic) medication will be documented. The nurse and ward doctor inspect the wound and dressing in accordance with routine care. Blood samples are taken at postoperative day one and three, and post-transfusion if applicable (Table 4). The timed up and go test (TUGT) is performed before discharge (Table 4). The TUGT will be administered in all patients who are able. If no weight bearing is allowed or patients are physically unable, than the test will be postponed to the outpatient visit. The mini mental state examination (MMSE) is administered for data stratification purposes [50–52], if patients are delirious during admission the MMSE is postponed to the outpatient visit.

In order to document experiences with CFC therapy all treatment patients will fill in a questionnaire at discharge, which is specifically drafted for this study (Table 5). During the study a booklet will be made available into which staff can write down prevalent occurring technical GRS-related problems.

**Table 5 Tab5:** Patient questionnaire

1. Did you feel that the pain reduced when treated with cryocompression therapy?	A	B	C	D	E
2. Would you rather have cryocompression treatment than analgesic pain treatment?	A	B	C	D	E
3. The standard setting used was the coldest; did you like this temperature setting?	A	B	C	D	E
4. Did you request the temperature setting to be upped?	Y				N

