## Statistics

### Analysis of outcome parameters

All statistical analyses will be computed using the SPSS statistical package (IMB SPSS, Inc., Release 20.0.0.0, 64-bit edition). Statistical analysis will be performed according to the intention-to-treat principle. Baseline characteristics will be described in accordance with CONSORT guidelines [41] using means and standard deviation in case of normal distribution, and medians and interquartile ranges otherwise. Continuous variables will be checked for normality, visually and by using the Shapiro Wilk test. Our primary analysis focuses on the differences in NRS-pain scores between the study groups 24 h postoperative and will be analyzed by use of Student’s T or Mann–Whitney U tests in case of skewed distribution. To assess treatment effect over time, a mixed model analysis for repeated measures will be performed. This model allows missing data and adjustment for serious confounders and interactions. In case of skewed distributions and outliers non-parametric variants will be used (e.g. Mann Whitney U or Friedman tests). Secondary continuous outcome measures (EQ-5D-3L, SF-12, DRS-R-98 and hemoglobin) will be compared by use of Student’s t or Mann Whitney U tests. Ordinal variables will be analyzed using the Mann–Whitney test. Chi-squared tests will be performed in case of categorical variables. In case of important confounding, analysis will be adjusted to correct for these factors (by use of multiple regression analysis, linear or logistic). A *p*-value of < 0.05 will be considered statistically significant.

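### Delirium severity (DRS-R-98) is compared between arms only among patients who screen positive after randomisation, so a true benefit would be attenuated and could, under specific conditions, change sign

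*Protocol article*

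**What the plan says.** Randomisation comes early: "randomization stratified by center will be performed directly after surgery" (Randomization). DOS is then scored three times daily, and "in case of a DOS-score higher or equal to three, geriatricians diagnose and subsequently monitor delirium severity with the delirium rating scale revised 1998" (Cryocompression therapy and clinical measurements). Table 4, footnote c, repeats the condition for DRS-R-98: "administered when DOS ≥ 3". Scoring continues "on a daily basis or until the score drops below 12.25 out of 39", so the number of scores per patient also depends on the course of the delirium.

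Under Postoperative delirium the plan states that "DRS-R-98 scores are compared within and between groups, and newly started psychotropic medication is compared". Analysis of outcome parameters names the test: "Secondary continuous outcome measures (EQ-5D-3L, SF-12, DRS-R-98 and hemoglobin) will be compared by use of Student’s t or Mann Whitney U tests". The same section declares intention to treat, but no DRS-R-98 value is defined for a patient who never screens positive. The Aim section hypothesises that less pain under CFC will lower delirium incidence.

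On cognition, "The mini mental state examination (MMSE) is administered for data stratification purposes". Table 4 places the MMSE at discharge and at 6–8 weeks, and "if patients are delirious during admission the MMSE is postponed to the outpatient visit". The analysis section does not name the MMSE.

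**The concern.** Reaching DOS 3 is an event after randomisation that the trial expects treatment to change. Conditioning on it breaks the randomised comparison. If CFC keeps some patients below the threshold, the CFC patients who still have a score are not the counterparts of the control patients who have one. A t or rank test on the scored patients then mixes the effect on severity with the effect on who gets scored. Delirium severity is a named secondary objective, so such a result would be reported and read as evidence about the treatment.

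The MMSE raises a related problem. A stratifier should be fixed before treatment. This one is measured afterwards, and delirium, itself an outcome, decides when. Any treatment comparison within MMSE strata would condition on something treatment may have altered.

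**Working it through.** The protocol gives no figure for DRS-R-98, so there is none to reproduce. The calculations show what the planned comparison would return under stated assumptions.

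**Inputs.** From the protocol: 160 patients, 1:1, so 80 per arm; delirium incidence 45 % in hip fracture populations (Background). Assumed: 45 % stands in for the DOS ≥ 3 rate, with 30 % as an alternative; latent severity is N(0,1) in controls, and a score exists above a threshold c.

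**1. Control mean among the scored.** For 45 % positive, c = 0.126. Mean = φ(c)/P = 0.3958/0.45 = 0.880. SD among positives = √(1 + 0.126 × 0.880 − 0.880²) = 0.580 latent SD.

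**2. Uniform benefit of 0.30 SD in everyone.** The effective threshold becomes 0.426, and 33.5 % screen positive. Mean = 0.3644/0.3352 − 0.30 = 0.787. Visible difference: 0.787 − 0.880 = −0.092 latent SD, which is 31 % of the true effect. At 30 % positive it is −0.073 (24 %). A uniform 0.50 SD benefit shows as −0.145 (45 %) or −0.114 (30 %). The sign is kept and most of the effect is lost.

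**3. CFC prevents only the mildest 20 % of cases.** Positives fall to 0.8 × 45 % = 36 %, with threshold 0.358. Mean = 0.3741/0.36 = 1.039. Difference: +0.160 latent SD, or 0.160/0.580 = 0.275 SD among positives. CFC looks worse although nobody was harmed. On the same latent scale, compare +0.16 with the −0.09 of step 2.

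**4. The same in scale points (illustrative scores).** Of 80 controls, 36 are scored: 18 mild at 14 and 18 severe at 24. Mean = (252 + 432)/36 = 19.0. Suppose CFC prevents half the mild cases and lowers every remaining score by 1. Then 27 are scored: (9 × 13 + 18 × 23)/27 = 531/27 = 19.67. The scored-only difference is +0.67. Over all 80, with unscored patients set to 0, the mean falls from 684/80 = 8.55 to 531/80 = 6.64, a benefit of 1.91. If 25 % of mild cases are prevented, the scored-only difference is −0.29; if 75 %, +2.00.

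**5. Effect mainly on onset.** A simulation of 1,000,000 per arm assumed that treatment lowers incidence from 45 % to 27 %, severity SD 5 points, and onset–severity correlation 0.6. The scored-only difference was +1.05 points with no effect on severity, +0.55 with a true 0.5-point reduction and +0.05 with a true 1-point reduction. With correlation 0.3 and a 1-point reduction it was −0.46, so the sign is not bound to change.

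**6. MMSE strata.** A simulation assumed a cut at 24, delirium in 46 % against 37 %, and delirium worsening a functional outcome by 0.5 SD. If delirium also lowers the MMSE by 4 points, the overall benefit of +0.049 SD becomes −0.045 and −0.019 in the high and low strata. If delirium leaves the MMSE unchanged, the strata (+0.047, +0.051) agree with the overall +0.047.

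**The case against.** The strongest reply is that the plan never says in words that the test is restricted to screen-positive patients. It states intention to treat, and the handling of unscored patients could sit in an analysis plan that is not shown. That is fair as to coding. But the protocol itself fixes who is measured, lists DRS-R-98 as a continuous outcome for a t or rank test, and supplies no value for the others. Followed as written, the test runs on the scored patients.

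Other objections stand and limit the point. A reader might infer that the severity comparison will reverse. Steps 2 and 4 show otherwise: a uniform benefit only shrinks, and reversal needs prevention concentrated on mild cases or on onset. The reversal is also modest against the noise. With about 36 and 29 cases the standard error is √(1/36 + 1/29) ≈ 0.25 SD among positives, so 0.275 is roughly one standard error.

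A reader might also take about 72 of 160 patients with a score (45 % × 160) as the protocol's expectation. The 45 % describes delirium in hip fracture populations generally, not DOS ≥ 3 in this trial, which has its own exclusions.

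Nor is the delirium evidence as a whole compromised. DOS is scored in all patients, incidence is already a separate objective, and new psychotropic medication can be compared in everyone.

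On the MMSE, a reader might infer that a planned analysis is biased. No analysis names MMSE strata, so harm arises only where they are used for a treatment comparison, and reversal further requires delirium to depress the later score. The Randomization section explains why the MMSE is impractical on arrival. That justifies not measuring it then, but does not make a later value a baseline factor.

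**Conclusion.** The point holds for DRS-R-98 severity. The planned between-group test compares subsets selected after randomisation and does not estimate the effect of CFC on delirium severity. Under normal latent severity and an assumed 45 % screen-positive rate, about 0.09 of a true uniform 0.30 SD benefit would be visible. Preventing only the mildest 20 % of cases would make CFC look about 0.16 latent SD worse. Attenuation is the expected consequence of a uniform benefit; a change of sign is a possibility under the conditions above. The Discussion considers DRS-R-98 sensitivity and differences in geriatric care between hospitals, but not this selection.

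The MMSE point is conditional: it applies wherever MMSE strata would enter a treatment comparison.

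Both matters concern secondary outcomes. The primary NRS-pain analysis and its sample size are untouched. A few DOS scores may precede randomisation, since DOS is also recorded at baseline and enrolment may run to 6 h after surgery; this does not alter the conclusion.

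**What to change.** - Make the severity comparison peak postoperative DRS-R-98 in all randomised patients. Give those who never reach DOS 3 the lowest rank, and use a rank test stratified by the randomisation strata (centre and surgery group).
- Treat a patient with DOS ≥ 3 but no DRS-R-98 as missing, not as lowest rank. State how patients already positive at baseline are handled.
- Read the result alongside the delirium incidence comparison that is already an objective. Report severity among cases, with numbers scored per arm, as descriptive only.
- Do not stratify treatment comparisons by MMSE. Use variables taken before randomisation, DRAS (on admission) and NMS (at inclusion). DRAS measures delirium risk, so it is not a like-for-like substitute for a cognitive score. Keep the MMSE as a description or an outcome.

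The cost is wording; no new data are needed. The drawback is many ties at the lowest rank. The rank test can handle these, but the result then reflects incidence and severity together and should be described so.

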## Background

Hip fractures are one of the most important causes of long-term disability and a significant public health issue [1]. Incidence varies on a global scale [2, 3] but incidence is estimated to vary between 414 and 957 per 100,000 inhabitants in the USA [4]. Due to aging of the population in general a significant increase in hip fracture numbers is expected [5].

Hip fractures are a serious condition associated with high morbidity, one-year mortality rates up to 29 % [2, 4], severe pain [6, 7] and significant decline in functional status [8–11]. Less than 50 % of (semi-) independent living elders return to their pre-fracture habitat [11, 12]. Among the most serious of complications is the onset of delirium, which has a particular high incidence of 45 % in hip fracture populations [13–15]. Possibly because this condition is known to be extremely painful [15–18] and patients with pain are nine times more likely to develop a delirium [18–20] and furthermore take longer to ambulate and consequently, have longer length of stay [9].

Upon admission 40 % of hip fracture patients is anemic [21] and observed intraoperative blood loss is systematically underestimated; up to six-fold in excess in extracapsular fractures [22]. The continued postoperative decline in hemoglobin levels results from, among others, surgical site bleeding [22]. This yields a specifically high transfusion rate in this frail elderly patient category where use anticoagulants or thrombocyte aggregation inhibitors is relatively prevalent [23]. Besides (postoperative) surgical site bleeding, the fracture trauma and subsequent surgical stabilization procedure induce a inflammatory response causing leakage of plasma proteins and migration of inflammatory cells that lead to local peripheral vasodilatation and increased capillary permeability, ultimately causing edema [24]. Edema gradually develops during the first week post surgery, is more pronounced in intertrochanteric fractures and correlates well with reduced knee extension strength and functional performance [25, 26]. In an attempt to reduce edema and postoperative hemorrhaging compressive wound dressings are applied [27–29]. Dynamic pneumatic compressive devices not only reduce blood loss, edema and offer a better (hemo) dynamic profile in the deep venous and lymph system, it also exerts analgesic effects and reduces the inflammatory response when combined with a cryotherapy adjunct [30–35].

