### Sample size calculation

Sample size calculation is based on the primary outcome measure, NRS-pain at 24 h postoperatively. Subsequently, a mean NRS-pain score for postoperative day one was drawn from the Spaarne Gasthuis electronic patient dossier digital databanks and a standard deviation of 2.2 was calculated for pooled internal fixation and (hemi) arthroplasty for cervical and peritrochanteric fractures. The minimal clinical relevant difference for NRS-pain is 1.3 out of 10 [53]. The alpha was set at 5 % with a power of 90 % due to anticipated heterogeneity in regard to operating techniques, general care protocols but predominantly in regard to pain protocols between the participating centers (Table 2). An expected NRS failure rate of 10 % is anticipated together with expected missing data a drop out of 22.3 % is computed. The total number of included patients will be 160.

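### A within-group comparison of DRS-R-98 partly measures the rule that opens and closes the ratings, so it cannot support a statement about cryocompression (minor)

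*Protocol article*

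**What the plan says.** Four places in the protocol article bear on this.

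- **Outcome parameters, Postoperative delirium:** "DRS-R-98 scores are compared within and between groups". The sentence does not say which ratings form the within-group comparison.
- **Cryocompression therapy and clinical measurements:** DOS is scored three times daily, and "in case of a DOS-score higher or equal to three, geriatricians diagnose and subsequently monitor delirium severity" with the DRS-R-98, "on a daily basis or until the score drops below 12.25 out of 39".
- **Table 4, footnote c:** DRS-R-98 is "administered when DOS ≥ 3". The table places it on the day of surgery, at 24, 48 and 72 h, and at discharge.
- **Statistics, Analysis of outcome parameters:** "Secondary continuous outcome measures (EQ-5D-3L, SF-12, DRS-R-98 and hemoglobin) will be compared by use of Student’s t or Mann Whitney U tests", and "A *p*-value of < 0.05 will be considered statistically significant". No paired test is named for DRS-R-98.

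The abstract lists incidence, duration and severity of delirium among the secondary objectives.

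**The concern.** The window in which DRS-R-98 is observed depends on the outcome. It opens when a patient looks delirious and closes because a score is low. A comparison of first with last score inside one arm therefore picks up the rule as well as any real change.

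Comparing fixed days avoids most of that but has another fault: patients who have dropped below 12.25 leave the series, so later means describe those still delirious.

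Delirium may also resolve without cryocompression, and a within-arm test cannot separate that from an effect of the device.

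What is at stake is the reading of a secondary outcome. A significant fall in the treated arm could be presented as benefit. So could a fall that is significant in one arm and not in the other, which can arise merely because the arms contain different numbers of rated patients.

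**Working it through.** **1. Patients per arm.** The article gives no figure for the DRS-R-98 comparison, so the only plan figure to reproduce is the total sample size. With SD 2.2, difference 1.3, two-sided 5 % (sidedness assumed) and 90 % power, n per arm = 2 × (2.2 × 3.2415 / 1.3)² = 60.2, so 61. The t-based value is 62. Then 2 × 62 / (1 − 0.223) = 159.6, which agrees with "The total number of included patients will be 160". That is 80 per arm. The Background speaks of delirium, "which has a particular high incidence of 45 % in hip fracture populations", so about 0.45 × 80 = 36 rated patients per arm. Lower counts (20 patients, or 20 % of 80 = 16) were also tried.

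**2. Why a fall is built in.** A patient enters a first-to-last pair only if the first score is at least 12.25; otherwise rating ends at once. If rating later stops by the rule, the last score is below 12.25, so the difference is negative with certainty. The size of the artefact depends on how many patients stop by chance. For a patient of constant true severity m and day-to-day SD s, the chance per rating is Φ((12.25 − m)/s):

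- m = 16, s = 5: Φ(−0.75) = 0.227. Over 9 further ratings, 1 − 0.773⁹ = 0.90.
- m = 18, s = 4: Φ(−1.44) = 0.075. Over 4 further ratings, 1 − 0.925⁴ = 0.27.
- m = 22, s = 2: Φ(−4.9), practically zero.

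**3. Simulated rejection rate, first versus last, one arm.** There is no treatment effect and no time trend. Means, SDs and numbers of ratings are assumptions; the article gives none.

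Paired t-test, 80 per arm, between-patient SD 4, 3,000 runs per row:

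| Mean | Day-to-day SD | Ratings | Share rated | Rejects |
|---|---|---|---|---|
| 18 | 4 | 5, no stop rule | 45 % | 5.6 % |
| 16 | 4 | 5 | 45 % | 73 % |
| 18 | 4 | 5 | 45 % | 52 % (mean change −2.2) |
| 18 | 3 | 5 | 45 % | 29 % |
| 18 | 2 | 5 | 45 % | 12 % |
| 20 | 4 | 5 | 45 % | 28 % |
| 22 | 3 | 5 | 45 % | 9 % |
| 22 | 2 | 5 | 45 % | 5 % |
| 18 | 4 | 3 | 45 % | 25 % |
| 18 | 4 | 5 | 20 % | 25 % |

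Wilcoxon signed-rank test with the number of pairs fixed (rates good to a few percentage points):

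| Mean | Between / day-to-day SD | Ratings | 20 pairs | 36 pairs |
|---|---|---|---|---|
| 16 | 3 / 5 | 10 | 99 % | 100 % |
| 16 | 3 / 5 | 4 | 68 % | 95 % |
| 18 | 4 / 4 | 5 | 36 % | 56 % |
| 18 | 4 / 3 | 4 | 12 % | 25 % |
| 22 | 4 / 2 | 10 | 6 % | 8 % |

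The third row of the second table shows the effect of numbers alone: the same null gives 36 % in an arm with 20 pairs and 56 % in an arm with 36.

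**4. Fixed days.** First versus third rating among those still rated, flat severity: 5-12 %.

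**5. Spontaneous recovery.** With a true fall of 1 to 2 points per day in every patient and no treatment effect, first versus last rejects in 96-100 % of runs with the stop rule. For 1 point per day without the stop rule it is 98 %. This is a separate cause from the rating rule.

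**6. Between arms.** Comparing first-to-last change between two arms under the null rejects in 4.6-5.4 % of runs in all scenarios of the t-test set. That holds when both arms have the same severity and the same chance of being rated.

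**The case against.** The strongest reply is that no faulty test is actually specified. The Statistics section names only two-sample tests for DRS-R-98, and nothing says that first is paired with last. For NRS-pain the authors do spell out a within-group contrast (before and after treatment); for DRS-R-98 they do not, so the phrase may mean no more than a description of the course. Table 4 uses fixed time points, where inflation is small. The wording of the stop rule is itself ambiguous. The Discussion says that severity is rated on information covering 24 hours, which should damp chance dips and argues against a large day-to-day SD.

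Most of this stands, and it limits the size of the point. It does not make the comparison usable. Whichever ratings are paired, a within-arm change mixes the rating rule or the loss of recovered patients with natural recovery.

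A reader might infer that both arms are bound to show a significant fall. The documents do not support that: the near-certain figures need a mean close to 12.25, a large day-to-day SD and many ratings. A reader might also see a threat to the third hypothesis in the Aim, but that hypothesis concerns delirium incidence, not speed of resolution.

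**Conclusion.** The point holds in limited form and is minor. A planned within-group comparison of DRS-R-98 cannot support a statement about cryocompression, because the start and stop rules contribute to any first-to-last fall and natural recovery can supply the rest. From the rating rules alone, the false-positive rate runs from about 5 % to nearly 100 % for first versus last, and is about 5-12 % for fixed days. The range rests on assumed DRS-R-98 values and on reading 12.25 as a stop rule, so no single figure within it should be quoted as the error rate.

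The primary outcome and the sample size are not touched. Nor does the rating rule by itself invalidate the between-arm comparison, which kept about 5 % error under the null.

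**What to change.** Under Postoperative delirium, remove the within-group part of the DRS-R-98 comparison and say that courses within each arm are shown descriptively, without a test. Base any statement on recovery from delirium on a between-arm comparison of days with delirium, counted in all randomised patients, with 0 for those who never have it. This serves the duration objective already in the abstract and includes every randomised patient rather than only those who screened positive.

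The cost is one planned secondary comparison, from which no valid inference about treatment is lost. No new data are needed: days can be derived from the DOS and DRS-R-98 records already planned. As Table 4 carries both instruments only to discharge, the count should be labelled as in-hospital days.
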